## Statistical analyses

Analysis will follow standard principles for RCTs, using two-group comparisons on all participants on an intention-to-treat basis. Primary analyses will include all evaluable data. Sensitivity analyses will use imputation techniques to account for potential bias as a consequence of non-ignorable missing data during follow-up. The primary comparison H^1^ at 6 months will be based on the AHA and MUUL scores and will be between treatment groups using generalized linear models, with terms included to account for matching and, potentially, confounding variables such as baseline unimanual capacity. Secondary analyses will use similar methods to compare the outcomes between groups for participation (domains of LIFE-H) and QOL (domains of CP-QOL). Where continuous data exhibit skewness not overcome by transformation, non-parametric methods (e.g. Mann–Whitney U Test) will be used for simple comparisons.

For H^2^: The magnitude of central neurovascular changes between groups will be determined using quantitative analysis of fMRI statistical parametric maps will be performed using *iBrain*™: regions of interest will be delineated for each individual (primary motor cortex PM1, supplementary motor area (SMA), and ipsilateral motor cortex (PM1ipsi) and active voxels in those regions will be counted. These data will be compared for each region over time using generalised estimating equations approach. In subjects where mirror movements did not occur, lateralisation between ipsilateral and contralateral PM1 will be assessed using an objective approach^CIC#188^ to determine the incidence and magnitude of brain reorganisation. Statistical significance will be at p<0.05.

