**Methods and analyses:**

A total of 50 children (25 in each group) with congenital hemiplegia will be recruited to participate in this randomized comparison trial. Children will be matched in pairs at baseline and randomly allocated to receive an intensive block group hybrid model of combined mCIMT followed by intensive bimanual training delivered in a day camp model (COMBiT; total dose 45 hours direct, 10 hours of indirect therapy), or a distributed model of standard occupational therapy and physiotherapy care (SC) over 12 weeks (total 45 hours direct and indirect therapy). Outcomes will be assessed at 13 weeks after commencement, and retention of effects tested at 26 weeks. The primary outcomes will be bimanual coordination and unimanual upper-limb capacity. Secondary outcomes will be participation and quality of life. Advanced brain imaging will assess neurovascular changes in response to treatment. Analysis will follow standard principles for RCTs, using two-group comparisons on all participants on an intention-to-treat basis. Comparisons will be between treatment groups using generalized linear models.

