## Methods and analyses

A matched pairs randomised comparison trial will be conducted to evaluate whether a novel rehabilitation model (COMBiT) will be more effective than conventional standard care (OT) for improving upper limb function in children with congenital hemiplegia.

The primary hypothesis to be tested is:

H^1^ COMBiT will reduce activity limitations (improve unimanual capacity and bimanual performance) to a greater extent than standard care.

The secondary hypotheses are:

H^2^ Use dependent neuroplasticity and neurovascular changes (fMRI) will be more extensive and retained for a longer duration in children undertaking COMBiT than those engaged in standard care.

H^3^ COMBiT will be more effective compared with standard care to increase participation and enhance quality of life.

Two broad aims will be addressed:

The primary aim of our study is to determine which model of upper limb training leads to greater changes in upper limb activity performance and whether changes are maintained to six months post intervention.

A secondary aim is to further our understanding of the central neurovascular mechanisms underlying changes in upper limb function according to the type of training applied. Improving our understanding of the mechanisms underpinning treatment efficacy is an essential next step towards providing effective treatment and sustained outcomes. In addition, understanding the nature and timing of the brain lesion and relationship to treatment response may assist with effective allocation of resources.

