### Sample size

The primary basis for sample size calculation for this study is adequate power for the primary hypothesis: H^1^ comparison between the functional effects of COMBiT compared to standard care at 26 weeks. Based on data from the previous study [25] a mean difference of 7 units (10% of the control group mean at baseline on the Melbourne Assessment of Unilateral Upper Limb Function (MUUL) is proposed as the minimum difference likely to have clinical implications [27,28]. We assume a standard deviation of 9 units. Based on a comparison with alpha = 0.05 and 80% power, 25 subjects in each group (n=50) are required.

For H^2^, our previous upper limb has shown 90% success on 3 repeated fMRI scans [25]. Using 3T fMRI we can see activation in the representative cortex for motor studies with good signal to noise ratio. We allow for some loss of information due to subject refusal (10%) and scans where motion is a confounder (10%). With 40 participants in an analysis of baseline to week 13 changes on fMRI, this study will have 80% power to detect a difference between groups of 0.9 SDs. If we consider the supplementary motor area (SMA) given coefficients of variation (COV) for control subjects performing motor tasks (COV of 11% in PM1 and 35% in SMA) [29] and activation signal of 1.5%, we are able to detect differences in percentage activation levels over time as small as 0.47.

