## Primary outcomes

There will be a primary outcome measure for upper limb bimanual co-ordination (the Assisting Hand Assessment) and unimanual capacity (The Melbourne Assessment of Unilateral Upper limb Function).

a) Bimanual performance

(i) Assisting Hand Assessment (AHA)

The AHA is a Rasch analysed measure of bimanual hand performance [73]. The AHA is a performance measure and examines the effectiveness with which a child with a unilateral impairment spontaneously or typically uses their impaired hand in bimanual activities [73]. The test yields a range of scores between 22 and 88 which are subsequently scaled by transforming the total raw score to a percentage and range from 25 to 100. Conversion of these ordinal scores into logits (log odds probability units) which are equal interval measures is possible through Rasch analysis. Inter-rater and intra rater reliability is high for summed scores (ICC 0.98 and ICC 0.99 respectively). There are three versions of the AHA; small kids, school kids and an adolescent version. Test-retest reliability is high for small kids and school kids (ICC 0.99 and 0.98 respectively.) The AHA has demonstrated it is responsive to change in many clinical studies [16,22,24,74,75]. Reliability studies yielded a smallest detectable difference (SDD) of 3.89 raw scores for the small kids and 3.65 raw scores for the school kids version [76]. For this study, the AHA will be scored by two certified raters whom will be masked to group allocation and order of assessment. Scores will be transformed into logits for ease of interpretation.

b) Unimanual capacity

i. The Melbourne assessment of Unilateral Upper Limb function (MUUL)

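### H1 rests on two unranked primary outcomes (AHA and MUUL) with one 0.05 threshold and no either/both rule, while the 80% power claimed for H1 was calculated for MUUL only

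*Protocol article*

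**What the plan says.** All places are in the protocol article.

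- **Outcomes.** The abstract says "The primary outcomes will be bimanual coordination and unimanual upper-limb capacity". The Primary outcomes section names the instruments: "There will be a primary outcome measure for upper limb bimanual co-ordination (the Assisting Hand Assessment) and unimanual capacity", the latter measured by the MUUL. Neither is ranked above the other.
- **Hypothesis.** Under Methods and analyses, H1 is one hypothesis covering both constructs: "COMBiT will reduce activity limitations (improve unimanual capacity and bimanual performance) to a greater extent than standard care".
- **Analysis.** The Statistical analyses section says "The primary comparison H^1^ at 6 months will be based on the AHA and MUUL scores". The only significance rule there is "Statistical significance will be at p<0.05", which closes the paragraph on H2. It gives no order of testing, division of alpha or composite, and does not say whether one or both outcomes must be significant.
- **Sample size.** The section opens with "The primary basis for sample size calculation for this study is adequate power for the primary hypothesis", identified as H1 at 26 weeks. The target is "a mean difference of 7 units (10% of the control group mean at baseline on the Melbourne Assessment of Unilateral Upper Limb Function (MUUL", with an assumed standard deviation of 9 units. It concludes: "Based on a comparison with alpha = 0.05 and 80% power, 25 subjects in each group (n=50) are required". No target difference, standard deviation or power is given for AHA.

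**The concern.** One hypothesis is attached to two outcomes, one alpha and one power figure, and the power figure comes from only one of the outcomes. H1 can be decided in two ways, and each leaves one stated figure unsupported.

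- If a significant result on either outcome confirms H1, 5% is not the error rate of H1.
- If both outcomes must be significant, the error rate is safe, but power computed for MUUL alone is not the power of H1.

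With 50 children, a split result (one outcome significant, the other not) is a realistic possibility. The article does not say whether that would confirm H1. If this is settled after the data are seen, the trial's main conclusion depends on a choice that could have been fixed in advance.

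**Working it through.** **Inputs from the Sample size section:** MUUL difference 7, SD 9, so d = 7/9 = 0.778; alpha 0.05; power 80%; 25 per arm. Sidedness is not stated; two-sided is assumed.

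**Inputs assumed, because the article gives none:** the correlation between the AHA and MUUL test statistics (range shown); the AHA effect (taken as the same standardised 0.778); the correlation between baseline and follow-up scores (0.5 to 0.7, only where adjustment is considered).

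**Step 1. Reproduce the stated sample size.**
n per arm = 2 × (9/7)² × (1.960 + 0.842)² = 25.95, so 26, against 25 stated. A one-sided test would need 21, which does not fit. The t-test version needs 27. At 25 per arm, power is 78.5% (normal) or 76.9% (t-test). The stated figure is thus reproduced to within rounding. It spends the whole two-sided 0.05 on MUUL: at 0.025 the same formula gives 32 per arm, so no alpha was set aside for AHA.

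**Step 2. Either outcome may carry H1: false-positive rate.**
For independent outcomes, 1 − (1 − 0.05)² = 9.75%. For correlated outcomes, 1 − P(|Z₁| < 1.96 and |Z₂| < 1.96) under a bivariate normal:

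| Outcome correlation | Any two-sided error | Error in favour of COMBiT only |
|---|---|---|
| 0 | 9.75% | 4.9% |
| 0.5 | 9.1% | 4.5% |
| 0.7 | 8.3% | 4.2% |
| 0.8 | 7.8% | 3.9% |
| 0.9 | 7.0% | 3.5% |

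The single-test references are 5% and 2.5%.

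**Step 3. Both outcomes required: power of H1.**
There is no alpha inflation. Joint power is P(Z₁ < q and Z₂ < q), where q is the normal quantile of the power for each outcome.

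| Power per outcome | Corr. 0 | Corr. 0.5 | Corr. 0.7 |
|---|---|---|---|
| 76.9% (t-test, 25 per arm, unadjusted) | 59% | 64% | 67% |
| 80% (as stated) | 64% | 69% | 71% |
| 87.5% (adjusted, baseline correlation 0.5) | 77% | 79% | 81% |
| 96.5% (adjusted, baseline correlation 0.7) | 93% | 94% | 94% |

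Adjustment is modelled by dividing d by √(1 − r²): 0.778/√0.75 = 0.898 at r = 0.5, and 0.778/√0.51 = 1.089 at r = 0.7.

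**Step 4. Cost of splitting alpha.**
At 0.025, the first step of Holm, MUUL power with 25 per arm is 67% unadjusted (t-test). With the same baseline adjustment it is 80% (r = 0.5) to 93% (r = 0.7).

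**The case against.** The strongest objection is that the only wording of H1 is conjunctive. A reader might infer that each outcome is tested separately and that one success is enough, so that the error rate of H1 nearly doubles. The article does not say that. No sentence lets AHA or MUUL alone confirm H1, and the 0.05 sentence ends the H2 paragraph. The near-doubling also needs uncorrelated outcomes, which is unlikely when both measure function involving the same impaired limb in the same children. This stands: 9.75% is the top of a conditional range. What remains is that the conjunction is never stated as a decision rule, so the either-outcome reading is left open.

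A second tempting inference is that, if both outcomes are needed, the 80% is simply wrong. The documents do not support that either. The Statistical analyses section allows for baseline unimanual capacity as a possible covariate, and with effective baseline adjustment joint power could reach or exceed 80%. But adjustment is only a possibility there, the baseline correlation is not given, and the Sample size section does not use it. The 80% is therefore unsupported for H1, not shown to be false.

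A third objection is that a statistical analysis plan commonly sets the multiplicity rule, and an article condenses. That is fair as regards the missing procedure. It does not remove the mismatch inside the article, which claims power for a two-outcome hypothesis from a one-outcome calculation.

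**Conclusion.** The point holds in a conditional form. The article fixes two unranked primary outcomes, one alpha and one power figure for H1, and the power figure covers only MUUL. Alpha 0.05 and 80% power cannot both be shown to describe H1.

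The size depends on the rule that the article leaves unstated. If either outcome suffices, the error rate is 7.0% to 9.75% for assumed outcome correlations of 0.9 to 0. If both are required, which is closer to the wording of H1, the error rate holds and the sample size inputs give joint power of about 59% to 67% for correlations 0 to 0.7, or about 77% to 94% with assumed baseline adjustment. Every joint figure assumes that AHA has the standardised effect of MUUL; a smaller AHA effect would lower them.

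**What to change.** Before unmasking, make two wording changes.

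1. In Statistical analyses, state one decision rule for H1. One option is that both AHA and MUUL must reach two-sided 0.05, which fits H1 as worded. The other is Holm across the two at an overall two-sided 0.05, with a separate claim for each outcome; H1 should then be reworded to match.
2. In Sample size, say that the 80% refers to MUUL alone. Add the power of H1 under the chosen rule, with the assumed AHA effect, the outcome correlation and any baseline adjustment.

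No extra visits or measurements are needed, and no extra children if the restated power is accepted. The cost is a less favourable stated power: under the both-required rule, the unadjusted joint figures above; under Holm, MUUL power of 67% unadjusted at the 0.025 step. If 80% joint power were wanted without relying on adjustment, about 35 per arm would be needed with independent outcomes, because each outcome would then need √0.80 = 89.4% power.

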### Randomisation

Following baseline assessments, children will be randomised within matched pairs to receive either COMBiT or standard care. To maximise homogeneity of the sample and minimise group differences at baseline, matching in pairs will be completed according to age (12 month bands), gender, and Manual Ability Classification System (MACS) level [30]. Treatment allocation will be recorded on a piece of folded paper inside a concealed opaque envelope. Using a sequence of computer-generated random numbers the number “1” or “2” will be allocated to each member of the pair. As each pair is randomised, they will be allocated the next consecutive envelope, which will be opened by non-study personnel who will read and record the treatment allocation. Study personnel will be informed of group allocation.

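### The primary model commits to the matching but leaves adjustment for baseline optional, with no baseline AHA term named, and the non-parametric fallback ignores the pairs

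*Protocol article*

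**What the plan says.** All statements are in the protocol article.

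- **Randomisation:** "Following baseline assessments, children will be randomised within matched pairs to receive either COMBiT or standard care". Pairs are formed on age band, gender and MACS level, not on baseline AHA or MUUL.
- **Primary outcomes:** AHA (bimanual) and MUUL (unimanual) are both primary.
- **Statistical analyses, primary model:** the six-month comparison of both scores uses generalized linear models "with terms included to account for matching and, potentially, confounding variables such as baseline unimanual capacity".
- **Statistical analyses, fallback:** for continuous data whose skewness survives transformation, "non-parametric methods (e.g. Mann–Whitney U Test) will be used for simple comparisons".
- **Sample size:** the target for the MUUL is "a mean difference of 7 units (10% of the control group mean at baseline", and an SD of 9 is taken. From these inputs the section concludes: "Based on a comparison with alpha = 0.05 and 80% power, 25 subjects in each group (n=50) are required". No within-pair or baseline-to-follow-up correlation is given.

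**The concern.** Three features of the stated analysis are fixed badly.

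1. **Baseline adjustment is optional.** The qualifier *potentially* applies to the covariates beyond the matching term, and no rule says when they enter. The reason offered is confounding. Under randomisation the main reason to adjust for baseline is precision. A confounding rationale invites a decision based on the imbalance that happens to be observed.
2. **The only example covariate suits one of the two primary outcomes.** Baseline unimanual capacity belongs with the MUUL. Nothing commits the AHA model to baseline AHA, and the matching factors do not supply it.
3. **The named fallback is a two-sample test.** Mann–Whitney treats the arms as independent samples, whereas allocation is within pairs. It also makes no use of baseline.

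At stake are power that the trial could have from data it already collects, and a primary model that can be chosen after the results are seen.

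**Working it through.** **Inputs from the Sample size and Randomisation sections:** difference 7, SD 9, alpha 0.05 (two-sided assumed, as sidedness is not stated), 25 per group, hence 25 pairs. **Assumed, because the document gives neither:** within-pair correlation of the outcome, ρ, from 0 to 0.5; baseline-to-26-week correlation, r, of 0.5 or 0.7. The SD of 9 is taken as that of the 26-week score, which the text does not specify.

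**1. The plan's own figure.** n per group = 2(1.960 + 0.842)² × 9²/7² = 25.9, so 26 against the stated 25. Power at 25 per group: 7/(9√(2/25)) = 2.750, and 2.750 − 1.960 = 0.790, giving 78.5% (77% with the t distribution). The figure reproduces to within one child per group. It is an unpaired, unadjusted calculation and takes no credit for matching or baseline.

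**2. Matching alone, as committed.** The SD of a within-pair difference is 9√(2(1 − ρ)) and its standard error is that divided by √25. Under the null, a paired analysis stays near 5% at every ρ. The Mann–Whitney columns come from simulating 25 normal pairs, 20,000 runs per setting.

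| ρ | SD of difference | Paired t power | Mann–Whitney power | Mann–Whitney type I error |
|---|---|---|---|---|
| 0 | 12.73 | 75% | 74% | 4.8% |
| 0.2 | 11.38 | 84% | 76% | 2.9% |
| 0.3 | 10.65 | 88% | 77% | 1.9% |
| 0.5 | 9.00 | 96% | 80% | 0.7% |

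With positive within-pair correlation, Mann–Whitney is conservative and less powerful. With none, the two tests hardly differ.

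**3. Baseline on top of matching.** Adjustment multiplies the SD of the difference by √(1 − r²), taking the same ρ for baseline and residual. At ρ = 0.2:
- r = 0.5: 11.38 × 0.866 = 9.86
- r = 0.7: 11.38 × 0.714 = 8.13

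Simulated power (6,000 runs per setting):

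| ρ | r | Matching only | Matching and baseline |
|---|---|---|---|
| 0.2 | 0.5 | 84% | 91% |
| 0.2 | 0.7 | 84% | 98% |
| 0.5 | 0.5 | 96% | 99% |

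Type I error was about 5% for both models.

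**4. The open choice.** If an analyst fitted the matched model with and without baseline and reported whichever was significant, simulated type I error at ρ = 0.2 would be about 7% for r = 0.5 and about 8% for r = 0.7. This is the worst case of selective choice; the document does not say that anyone will do this.

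**The case against.** The strongest reply is that the primary model is sound. It commits to matching terms, and *potentially* qualifies only the further covariates. That stands. A reader might infer that the primary comparison has the wrong error rate for a matched-pairs trial, but the stated model holds about 5% with or without baseline, provided the covariates are fixed in advance.

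A reader might also infer that skewed primary data will be switched to Mann–Whitney. The text gives that test as an example and limits it to simple comparisons. It neither says that it replaces the primary model nor excludes the primary outcomes. Where it ignores positive pairing it errs on the conservative side, so it does not raise the risk of a false positive.

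The gain from baseline should be measured against the planned matched analysis, not the unpaired 77%. At r = 0.5 that makes it 7 points at ρ = 0.2 and 3 points at ρ = 0.5. Omitting baseline does not take power below the basis on which the trial was sized.

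A further tempting inference is that losing one child discards the partner's data. That would need fixed pair effects, which the article does not specify, and an attrition rate for the primary outcomes, which it does not give.

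Finally, an article may leave a full covariate list to an analysis plan, and the wording *such as* marks an example. This answers only part of the point. The article does describe its primary model, makes the main prognostic covariate optional on a confounding rationale, and names an unpaired test for a paired design. Those are statements made, not details left out.

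**Conclusion.** The point holds as one of precision and pre-specification. Baseline adjustment is optional, baseline AHA is not committed for a primary outcome, and the named fallback ignores the pairing. The validity of the matched model is not in question once its covariates are fixed.

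The size depends on correlations that the document does not give. Adding baseline to matching is worth about 3 to 14 points of power over the settings tabulated: least at ρ = 0.5 with r = 0.5 (96% to 99%), most at ρ = 0.2 with r = 0.7 (84% to 98%). If Mann–Whitney were used on a primary outcome at ρ = 0.3, power would be about 11 points lower than with a paired t-test (77% against 88%), at a true error rate near 2%. The calculations assume normal data, complete pairs, and an SD of 9 for the 26-week score. If that SD already refers to change from baseline, the gain from adjustment would be smaller. They use the MUUL inputs; no AHA difference or SD is given, so the size for AHA cannot be computed.

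**What to change.** In the Statistical analyses section:

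1. Delete *potentially*, and state that each primary model includes the matching term and the baseline value of the outcome being analysed (AHA for AHA, MUUL for MUUL).
2. Give precision, not confounding, as the reason for adjusting.
3. Replace Mann–Whitney with a method that respects the pairs, such as the Wilcoxon signed-rank test on within-pair differences or a within-pair permutation test. For a primary outcome, label it a sensitivity analysis beside the adjusted model.

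The cost is analysis wording only. Both scores are already primary measures and baseline assessments precede randomisation, so no new data, visits or participants are needed. The change should be recorded before outcome data are seen by treatment group.

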### Inclusion criteria

The study will include school aged children and youth:

(1) With a confirmed diagnosis of congenital hemiplegia.

(2) Aged five to 16 years.

(3) Who have reduced upper limb function due to predominant spasticity rather than dystonia.

(4) Who can provide sufficient co-operation and cognitive understanding to participate in the therapy activities.

For a subset of children performing the Advanced Brain Imaging studies further inclusion criteria are:

i Sufficient co-operation to perform Advanced Brain Imaging studies for 45 minutes.

ii No exclusions for 3 Tesla Magnetic Resonance Imaging (3T MRI) including no metal implants, no shunts, no uncontrolled epilepsy as the later would be a confound.

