Children with sufficient comprehension will also complete an additional complex motor task in the scanner. This is a timing versus sequencing task performed in a block design (two runs of six minutes each), where the subject alternates between a block of single index finger button pressing with a block of random sequences of 3-finger button presses. For the sequence task, visual cues of “123, 321, 213” numbers to denote a random sequence of pushing three buttons with their index, third and fourth fingers with their dominant hand. This complex task is designed to differentiate activation in the primary motor cortex and different aspects of the basal ganglia circuit. The rationale behind the simple and complex movement is based on previous studies that showed these movements are able to induce activation of the motor cortex and basal ganglia circuits [44]. Notably increased complexity of finger movements increases activation of the basal ganglia circuit, and thus provides an ideal model to utilise fMRI to locate function specific regions of the cortex associated with finger movements.

An additional five minutes of resting-state fMRI will also be collected for analysis of functional connectivity immediately after the motor tasks. Tasks performed prior to resting-state fMRI can influence functional connectivity [45], so the resting-state data will be collected after the motor paradigms have been completed to provide consistency. The whole assessment will take no longer than 50 minutes in the scanner. The actual movements performed in the scanner will be rated for speed, the range of motion actually performed, ability to isolate the movement and presence of mirror movements in the contralateral hand or general body movements for the active motor task and the number and timing on correct button sequences in the complex motor task.

Functional MRI will be acquired using a BOLD acquisition sequence (Gradient-recalled-echo (GRE) echo-planar imaging (EPI), Repetition Time (TR)=3.0s, Echo Time (TE)=30 ms, Flip angle = 85°, Slice thickness=3 mm, FOV=216 mm, 44 slices, 72 × 72 matrix yielding an in-plane resolution of 3.0 mm × 3.0 mm). A single set of T2-weighted anatomical, FLAIR and 3D T1 volumes will also be collected. Functional MRI image processing, analysis and visualisation will be performed using iBrain™ software [41], SPM8 analysis software (Wellcome Department of Imaging Neuroscience, London, UK) and the iBrain™ Analysis Toolbox for SPM [46].

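### The 0.47 detectable difference given for H2 is in percentage-activation units, but the planned H2 analysis counts active voxels, so the figure does not describe that test

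*Protocol article*

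**What the plan says.** The Sample size section powers H2 on a standardised difference. "With 40 participants in an analysis of baseline to week 13 changes on fMRI", it states, "this study will have 80% power to detect a difference between groups of 0.9 SDs". The 40 comes from the 50 randomised children after 10% for refusal and 10% for motion. The section then takes the supplementary motor area (SMA) as an example, with a coefficient of variation (COV) of 35% from control subjects and an activation signal of 1.5%, and concludes that "we are able to detect differences in percentage activation levels over time as small as 0.47".

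The Statistical analyses section defines what will be compared under H2. Regions of interest are delineated for each child, "active voxels in those regions will be counted", and the counts are compared by region over time with generalised estimating equations (GEE). The significance rule is "Statistical significance will be at p<0.05".

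Two other parts of the article bear on this. Inclusion criteria limits imaging: "For a subset of children performing the Advanced Brain Imaging studies further inclusion criteria are". The criteria that follow are co-operation for 45 minutes and no 3T MRI exclusion (implants, shunts, uncontrolled epilepsy). Neurovascular measures justifies the two scanner tasks as ones these children often find hard and that should respond to training. It then describes the complex task as "pushing three buttons with their index, third and fourth fingers with their dominant hand".

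**The concern.** A reader who wants to know how sensitive the H2 test is will take 0.47, the only figure in interpretable units. If the analysed variable is a different one, that figure says nothing about the planned test. A count of voxels above a threshold depends on the threshold, the size of the region drawn and the noise. Its variability cannot be inferred from that of percentage signal.

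Two inputs also lack support: the SD used for a change, and the number of children who can be scanned. If H2 gives a null result, readers will need to know what size of difference the test could have found, and at present they could not tell.

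The hand used in the complex task is a separate question of what is measured. H2 concerns use-dependent change, so activation from the unimpaired hand would not directly reflect change in the trained limb.

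**Working it through.** **Inputs from the article.** 50 children, 25 per arm; losses of 10% and 10%; 40 analysed (20 per arm assumed); effect 0.9 SD; power 80%; alpha 0.05 (two-sided assumed); SMA COV 35%; signal 1.5% (Sample size; Statistical analyses).

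**1. Reproducing the plan's figures.**
- Number analysed: 50 × (1 − 0.10 − 0.10) = 40.
- Detectable difference at 20 per arm, normal approximation: (1.960 + 0.842) × √(2/20) = 0.886 SD. With the noncentral t it is 0.909 SD. Both round to 0.9.
- Power at 0.9 SD: 81.2% (normal) or 79.2% (noncentral t).
- SMA translation: SD = 0.35 × 1.5 = 0.525, and 0.9 × 0.525 = 0.4725, the stated 0.47.

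The arithmetic is right, and it shows that 0.47 is in percentage-signal units.

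**2. Does it carry over to the planned endpoint?** The 0.9 SD does, if 40 children are analysed and change in voxel count is roughly normal. The 0.47 does not. Converting 0.9 SD to voxels needs the SD of change in the count, and the article gives no mean, SD or COV for counts. No replacement figure can be computed from it.

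**3. The SD behind 0.47 on its own scale.** The contrast is change from baseline to week 13. If the COV is between-subject (assumption), SD of change = 0.525 × √(2(1 − r)), where r is the test-retest correlation. The detectable difference is then 0.9 × 0.525 × √(2(1 − r)):

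| r (assumed) | Detectable difference |
|---|---|
| 0 | 0.67 |
| 0.25 | 0.58 |
| 0.5 | 0.47 |
| 0.75 | 0.33 |

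The stated value corresponds to r = 0.5, which the article does not state.

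**4. Number analysed.** The 20% loss covers refusal and motion only. The share of children ineligible for 3T MRI is not given. With 10% or 20% ineligible (assumption) on top of the stated loss, 40 × 0.9 = 36 or 40 × 0.8 = 32 remain. Noncentral t, two-sided 0.05:

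| Analysed | Per arm | Detectable at 80% power | Power at 0.9 SD |
|---|---|---|---|
| 40 | 20 | 0.91 SD | 79% |
| 36 | 18 | 0.96 SD | 75% |
| 32 | 16 | 1.02 SD | 69% |

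**5. Hand used in the complex task (no arithmetic).** Neurovascular measures justifies both tasks by impairment and expected response to training. The same section assigns the button-press task to the dominant hand. Body functions and structures equates the unimpaired limb with the writing limb. Taken together, the complex task appears to use the unimpaired hand, and its stated rationale then does not fit it.

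**The case against.** The strongest reply is that H2 is powered on 0.9 SD, a scale-free quantity, and that 0.47 only illustrates it for one region. This stands. A reader might infer that the whole H2 power statement fails, but the documents do not support that, and the fault is confined to the translation.

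On the number scanned, a reader might infer that 40 is out of reach. That is not shown either. The article gives no eligible share, reports 90% success with repeated scans in earlier work, describes mock-scanner practice and cites 180 potential children on the register. The refusal allowance may also overlap with the co-operation criterion. What remains is that implants, shunts and epilepsy are neither refusal nor motion, and nothing is set aside for them.

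On the COV, it would be tempting to call 0.47 too optimistic. The article does not say whether the COV is between-subject or from repeat scans, and at a high correlation the true figure would be better than 0.47. The fault is an unstated assumption whose direction is unknown.

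Counting voxels is not itself an error. Motion is handled in preprocessing by realignment, motion covariates and nulling of affected scans, and an activation threshold may properly sit in a fuller plan.

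The dominant-hand task is an additional one for children with sufficient comprehension. It has its own stated purpose, and the H2 analysis text does not name it. It has no bearing on the power figures, and it does not show that H2 as a whole is measured on the wrong hand. The mismatch between rationale and description remains.

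**Conclusion.** The point holds in a limited form. The 0.9 SD with 80% power is sound if 40 children are analysed. The 0.47 is not the detectable difference of the planned test, because it is in percentage activation while the test uses voxel counts with no stated variance. This conclusion needs no outside assumption.

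Two qualifications rest on assumptions. On its own scale, the figure ranges from 0.67 to 0.33 for correlations of 0 to 0.75, if the COV is between-subject. Power at 0.9 SD falls to between 75% and 69% if 10% to 20% of children cannot be scanned.

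The conflict over the hand used in the complex task is a separate matter of what is measured.

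H2 is a secondary hypothesis and the trial is sized on H1, so this should be corrected but does not threaten the primary comparison.

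**What to change.** Put the H2 endpoint and its power on one scale, in one of two ways:

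- Make regional percentage signal change, from the task done with the impaired hand, the H2 endpoint. Analyse it in the planned GEE over time and keep voxel counts as supportive. The later time point should stay in the model, because H2 also claims longer retention and a week-13-only endpoint would drop that part.
- Or keep voxel counts, withdraw 0.47, and state the detectable difference only as 0.9 SD.

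In either case, restate power for the expected number of MRI-eligible children. Wherever a difference is given in absolute units, give the SD of change, or the COV with its type and an assumed test-retest correlation.

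Reconcile the task rationale and the dominant-hand description in Neurovascular measures with the definition of the unimpaired limb in Body functions and structures. Otherwise, label the dominant-hand task exploratory and keep it outside the H2 test.

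The cost is a change of wording and probably a less favourable H2 power figure. The scans and the sample stay the same.
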